### Study setting and recruitment

This study will be performed at Dongzhimen Hospital Affiliated to Beijing University of Chinese Medicine between October 2019 and June 2021. A total of 60 patients will be recruited through advertisements placed on social media and community centers. A 1-week baseline assessment will be needed before randomization. During the baseline assessment period, volunteers will provide relevant medical records of thyroid diseases and complete clinical evaluation. Subjects who meet the acceptance criteria and agree to join the study will further complete the baseline data and wait for the result of random grouping allocation. Subjects who cannot join the group for any reason will be given a full explanation and health guidance.

### Randomization and allocation concealment

The random number sequence will be generated with SPSS software version 23 (IBM Corp., Armonk, NY, USA) by an independent researcher who will be in charge of assigning eligible participants into two groups equally and randomly. The independent researcher will not participate in patient treatment, outcome evaluation, data collection, or data analysis. Opaque envelopes containing randomized serial numbers for grouping inside with numbers in order on the cover will be prepared and kept by the independent researcher who took no part in this trial. When the eligible participants sign the informed consent form, the clinical researcher will receive an envelope according to the sequence numbers from the independent researcher and attain the information of the group allocation.

### Blinding

Because of the particularity of acupuncture, it is difficult to blind clinical researchers and participants. In this study, only two data researchers in charge of the collection, preservation, and analysis of data are blinded. Participants will provide information to the date researchers through online questionnaires without communication between both sides. So that data researchers cannot be aware of the grouping allocation. In this study, the data of each participant will be collected every 8 weeks, hence the researchers also cannot infer the grouping allocation through data information. Data researchers will be asked to speculate the grouping allocation to evaluate the implementation of the blind method.

### Sample size estimation

This study aims to evaluate the clinical effectiveness and safety of PNHM for HT. The estimation of sample size should be based on the feasibility, precision about the mean, and variance [24]. It is stipulated that the sample size of exploratory trials is 20–30 per group in China [25]. With consideration of the drop rate of 20% and the feasibility of the study, we finally plan to recruit 60 participants in total to assure the validity of the mean and effect size.

### Intervention

The intervention protocol of this study is based on the consensus of experienced acupuncture practitioners and thyroid disease specialists. Acupuncturists who hold a TCM license will perform the treatment. Participants of both groups will undergo acupuncture treatment for 16 weeks at different stages of the study. The details of the PNHM are as follows and shown in Table 1.

**Table 1 Tab1:** Locations and manipulations of the acupuncture points selected in this study

Acupoints	Location	Size of needle	Manipulation
**San Jian (LI3)**	On the dorsum of the hand, in the depression radial and proximal to the second metacarpophalangeal joint.	0.25 × 40 mm	Insert the needle to a depth of 1–2 mm, adjust the direction of needle’s tip towards He Gu (LI4) and penetrate the needle horizontally within the subcutaneous tissue to a depth 0.8–1.0 cun (20.0 mm–25.0 mm). Manipulate needle to get “de-qi” sensation.
**He Gu (LI4)**	On the dorsum of the hand, radial to the midpoint of the second metacarpal bone.	0.18 × 40 mm	Same as “San Jian (LI3)”
**Qu Chi (LI11)**	On the lateral aspect of the elbow, at the midpoint of the line connecting LU5 with the lateral epicondyle of the humerus.	0.30 × 75 mm	Insert needle to a depth of 1–2 mm, adjust the direction of needle’s tip towards Bi Nao (LI14) and penetrate the needle horizontally within the subcutaneous tissue to a depth 2.5–2.8 cun (62.5 mm–70.0 mm). Manipulate needle to get “de-qi” sensation.
**Bi Nao (LI14)**	On the lateral aspect of the arm, just anterior to the border of the deltoid muscle, 7 B-cun superior to LI11	0.30 × 75 mm	Insert needle to a depth of 1–2 mm, adjust the direction of needle’s tip towards Jian Yu (LI15) and penetrate the needle horizontally within the subcutaneous tissue to a depth 2.5–2.8 cun (62.5 mm–70.0 mm). Manipulate needle to get “de-qi” sensation.
**Jian Yu (LI15)**	On the shoulder girdle, in the depression between the anterior end of lateral border of the acromion and the greater tubercle of the humerus.	0.25 × 40 mm	Insert needle obliquely to a depth of 0.8–1.5 cun (20.0 mm–37.5 mm). Manipulate needle to get “de-qi” sensation.
**Ren Ying (ST9)**	In the anterior region of the neck, at the same level as the superior border of the thyroid cartilage, anterior to the sternocleidomastoid muscle, over the common carotid artery.	0.25 × 40 mm	Insert needle perpendicularly to a depth of 0.8–1.5 cun. Manipulate needle to get “de-qi” sensation.
**Zu San Li (ST36)**	On the anterior aspect of the leg, on the line connecting ST35 with ST41, 3 B-cun inferior to ST35	0.25 × 40 mm	Insert needle perpendicularly to a depth of 1.0–1.5 cun (25.0 mm–37.5 mm). Manipulate needle to get “de-qi” sensation.

Acupoints: San Jian (LI3), He Gu (LI4), Qu Chi (LI11), Bi Nao (LI14), Jian Yu (LI15), Ren Ying (ST9), Zu San Li (ST36). All acupoints are positioned according to the WHO Standard Acupuncture Point Locations in the Western Pacific Region [26].

Needles: “Andy” disposable sterile stainless needles, size of 0.25 × 40 mm and size of 0.30 × 75 mm needles will be used in this trial.

Manipulation: With supine positions, San Jian (LI3) will be penetrated towards He Gu (LI4), Qu Chi (LI11) will be penetrated towards Bi Nao (LI14), Bi Nao (LI14) will be penetrated towards Jian Yu (LI15). Jian Yu (LI15), Ren Ying (ST9), Zu San Li (ST36) will be punctured to standardized needling depths. De-qi sensation (an irradiation feeling deemed to indicate effective needling) should be achieved in each acupoint. Every participant should take three times of treatment per week for 16 weeks, thus a total of 48 treatments, each treatment lasting for 20 min.

Penetration needling is a technique of point-through-point needling. The procedures are as follows: the needle is first being punctured into the skin to a depth of 1–2 mm, then the direction of the needle’s tip is adjusted towards the adjacent acupoint, and finally, the needle is penetrated horizontally within the subcutaneous tissue towards an appropriate depth according to the local anatomical structures.

### Outcomes and measurements

#### Primary outcomes

The primary outcome will be the change of the concentrations of serum anti-thyroperoxidase antibodies (TPOAb), serum anti-thyroglobulin antibodies (TgAb), and the concentrations of thyroid hormone, including total thyroxine (FT_4_), free thyroxine (FT_3_), and thyroid-stimulating hormone (TSH). Data will be collected before the start of the study (the baseline assessment) and at weeks 8, 16, 24, and 32.

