### Statistical analysis

Data of this clinical trial will be analyzed using SPSS version 23.0 software (released 2015, IBM Corp., Armonk, NY, USA). All data will be presented as mean ± standard deviation or value and its percentage. Demographic (age, sex, course, family history, the dosage of drugs) will be compared between two groups as the baseline assessment. The data of the observation indicators are all measurement data. According to the normal test, select the appropriate parameter test or non-parameter test. A paired *t* test or Wilcoxon signed-rank test can be used for comparison before and after treatment within group. Independent sample *t* test or Wilcoxon rank-sum test can be used for comparison between groups. In two groups, all the statistical tests will be performed with bilateral tests, and *P*< 0.05 indicates the difference deemed statistically significant.

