## Discussion

The current treatment of HT focuses mainly on the symptom of hypothyroidism that occurs in the later stage of the disease via orally-taken LT4 in a long-term. However, there are not yet any effective treatments for symptoms of neck pressure, fatigue, mood swings, infertility, and others. Comprehensive management methods adopted to delay the progression of the disease or reduce the degree of hypothyroidism deserve further exploration.

Acupuncture has advantages in alleviating clinical symptoms, such as neck pressure, fatigue, and mood swings, and hardly has side effects. Some studies also suggest that acupuncture can stimulate the body to produce a series of neurohumoral immune responses and as a result improve immune disorder state [32]. This suggests that acupuncture has potential therapeutic value for HT. The abovementioned acupuncture treatments can be referred to ancient acupoints for treating thyroid diseases and the experience of modern acupuncture experts. In our earlier clinical observations, this acupuncture method can improve clinical symptoms of HT patients, and some patients’ thyroid-related antibody concentrations have decreased.

Some studies suggest a positive correlation between antibody concentration and the extent of thyroid inflammatory cell infiltration [33, 34]. Thyroid antibody concentrations are also positively correlated with the quality of life of HT patients. Thus, we have chosen antibody concentration as one of the main efficacy indicators to objectively reflect the subject’s immune status. Meanwhile, we will also observe whether the TSH is further stabilized or decreased to the normal range, so as to potentially reduce the dose of FT4 with the help of acupuncture. The use of multiple symptom score scales as secondary efficacy indicators is to fully evaluate the effect of acupuncture treatment on clinical symptoms of HT patients.

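### Five analytes share the primary outcome with no lead analyte or visit, so testing each at P<0.05 gives about a 13-23% chance of a false-positive primary result at a single visit

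*Protocol article*

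**What the plan says.** The Primary outcomes section defines a single primary outcome with five components. Two are antibodies: "The primary outcome will be the change of the concentrations of serum anti-thyroperoxidase antibodies (TPOAb), serum anti-thyroglobulin antibodies (TgAb"). Three are thyroid function measures: "the concentrations of thyroid hormone, including total thyroxine (FT_4_), free thyroxine (FT_3_), and thyroid-stimulating hormone (TSH"). The abstract gives the same list. On timing the section says only: "Data will be collected before the start of the study (the baseline assessment) and at weeks 8, 16, 24, and 32". It singles out no visit.

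The Statistical analysis section plans separate two-sample comparisons (an independent-samples t "test or Wilcoxon rank-sum test can be used for comparison between groups") and paired tests within each group. On the threshold it says that "all the statistical tests will be performed with bilateral tests" and that a P value below "0.05 indicates the difference deemed statistically significant". It gives no order of testing, no adjustment, and no rule on whether one, all or a particular analyte must succeed.

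The Discussion does not supply a lead endpoint. It says "we have chosen antibody concentration as one of the main efficacy indicators", which leaves the antibodies as one indicator among several and does not choose between the two.

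**The concern.** When several measures are jointly primary and each is tested at 0.05, the 5% error rate applies to each test and not to the primary claim. With no named analyte, visit or success rule, whichever of the five crosses the threshold can be presented as the primary result after the data are seen.

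The three thyroid function measures make this worse. The inclusion criteria require thyroid hormone within the normal range on regular levothyroxine. The document states no direction of benefit for FT3 or FT4. With two-sided tests, a chance shift either way in measures that start normal could count as a significant primary finding.

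What is at stake is the meaning of a positive primary result. The Objective and Sample size estimation sections both state an aim to assess effectiveness, so the P values are not offered as purely descriptive.

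**Working it through.** **Plan's own figure.** The article states no family-wise error rate, power, effect size or standard deviation, so there is no error rate to reproduce. The planned size is 60, 30 per group, based on a convention of 20-30 per group and a 20% drop rate. Retention would be 30 × 0.8 = 24 per group, inside that range. This is consistent with the text but is not a power calculation.

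**Inputs from the article.** Five primary analytes (Primary outcomes). Post-baseline visits at weeks 8, 16, 24 and 32 (same section). Two-sided 0.05 for each test (Statistical analysis). Controls start their own acupuncture after week 16 (Study design).

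**Assumptions, because the article gives no figures.** All null hypotheses are true. Any one significant result is read as a positive primary result. The correlation between analytes, r_a, runs from 0 to 0.8. The correlation between visits, r_v, runs from 0 to 0.9. Correlated cases were simulated as multivariate normal test statistics with rejection at |Z| > 1.96.

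**One visit, five tests.** If independent: 1 − 0.95^5 = 1 − 0.774 = 22.6%. With equal correlation between analytes:

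| r_a | Chance of at least one P<0.05 |
|---|---|
| 0 | 22.6% |
| 0.3 | 20.8% |
| 0.5 | 18.3% |
| 0.7 | 14.9% |
| 0.8 | 12.7% |

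This gives about 13-23%.

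**Weeks 8 and 16, ten tests.** If independent: 1 − 0.95^10 = 1 − 0.599 = 40.1%. With correlation:

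| r_a | r_v | Chance of at least one P<0.05 |
|---|---|---|
| 0 | 0.5 | 38% |
| 0.5 | 0.5 | 31% |
| 0.5 | 0.7 | 29% |
| 0.5 | 0.9 | 25% |
| 0.8 | 0.9 | 17% |

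This gives about 17-40%.

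**All four visits, twenty tests, for illustration only.** If independent: 1 − 0.95^20 = 1 − 0.358 = 64.2%. At r_a = 0.5 the rate is 48% for r_v = 0.5, 42% for r_v = 0.7, 37% for r_v = 0.8 and 32% for r_v = 0.9.

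**Thresholds that would hold 5%.** Bonferroni over five analytes at one visit: 0.05/5 = 0.01. Over the two antibodies at one visit: 0.05/2 = 0.025, giving at most 1 − 0.975² = 4.9% if they are independent. One analyte at one visit stays at 0.05.

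The within-group before-and-after tests are not counted in any of these figures.

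**The case against.** The strongest objection is that this is a pilot. The abstract calls it one, the sample size rests on a convention for exploratory trials, and the Discussion says that the small sample may not show the true clinical effect. An unadjusted P value in such a study is arguably a matter for cautious reporting. This stands as a reason for lower severity. It does not remove the problem, because the same document states an effectiveness aim and sets a formal significance rule for all tests.

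A second objection is that a success rule or adjustment could sit in a full protocol or analysis plan that is not shown. That is possible. However, the five-part primary outcome and the 0.05 rule for all tests are what this document itself fixes, and an adjustment elsewhere would have to depart from that rule.

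Two stronger readings are tempting, and the document supports neither.

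- A reader might infer twenty primary tests and an error rate above 40%. The article says that data are collected at four visits, not that a primary between-group test is made at each. At weeks 24 and 32 controls are receiving acupuncture, so those visits do not compare treatment with no treatment. Even if all twenty tests were run, the rate falls below 40% at stronger assumed correlations (37% at r_a = 0.5 and r_v = 0.8).
- A reader might infer that a chance finding would be used to justify a larger trial. The abstract says only that the results will assist further analyses.

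**Conclusion.** The concern holds. Following the text as written, the chance of at least one false-positive primary result is at least about 2.5 times the nominal 5% (12.7/5 = 2.5): about 13-23% if one visit is tested and about 17-40% if both controlled-period visits are. It would be higher still if weeks 24 and 32 were added, with the caveat on what those visits compare.

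These figures rest on a global null, on any single significant result being read as positive, and on assumed correlations. The exact size is therefore uncertain, but no scenario examined comes near 5%. Given the pilot status, this is something that should be fixed; it is not a fatal defect.

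**What to change.** Before outcome data are examined:

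1. Name week 16 as the primary time point. It is the last assessment before controls start acupuncture.
2. Choose one of two structures. (a) Make TPOAb change the single primary outcome at 0.05, with TgAb tested only if TPOAb is significant; the Background treats TPOAb as the main basis of diagnosis. (b) Keep TPOAb and TgAb as co-primary with Bonferroni (0.025 each) or Holm adjustment. Option (b) fits the trial's own diagnostic criteria better, because they accept any elevated thyroid antibody, so patients without raised TPOAb may enrol.
3. Make FT3, FT4 and TSH secondary or safety measures.
4. Report all other comparisons as estimates with 95% confidence intervals and no significance claim.

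**Cost.** Fewer results can be called significant. Under (a) the TPOAb test loses no power. Under (b), with 24 per group retained and 80% power, the normal approximation (z for alpha + z for power) × √(2/24) gives a detectable difference of (1.960 + 0.842) × 0.289 = 0.81 SD at 0.05 and (2.241 + 0.842) × 0.289 = 0.89 SD at 0.025. The Trial status section says that recruitment is under way, so the change needs a dated, disclosed amendment to the protocol and the registry entry. It should state that no outcome data had been examined.

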#### Secondary outcomes

The secondary outcome measurement includes 3 scales. Data will be collected before the start of the study (the baseline assessment) and every 8 weeks in the whole process.

##### Thyroid-related quality of life questionnaire short-form (ThyPRO-39) [27, 28]

The ThyPRO is a questionnaire of 85 items, widely used to evaluate thyroid-related symptoms and health quality of life. ThyPRO-39, a shorter version of ThyPRO, is a self-assessment scale of 39 items, using Likert 5-point scale. It has 12 subscales, further divided into 3 categories. According to the extent of thyroid disease’s impact in the past 4 weeks, every question can be rated on 0, 1, 2, 3, or 4 points, respectively, not at all, a little, some, quite a bit, or very much. Scores for each subscale need to be converted into standard points according to the score table and calculation formula, and standard total score can be calculated, ranging from 0 to 100 points. A higher score indicates a worse quality of life. ThyPRO-39 is used to evaluate the influence of HT on patient quality of life. Data will be collected before the start of treatment (the baseline assessment) and at 8 and 16 weeks after randomization.

##### The Mos 36-item Short Form Health Survey (SF-36) [29, 30]

SF-36 is the most widely used quality of life assessment tool, containing 36 items, covering nine variables. For each variable item, scores are coded, summed, and transformed on to a scale from 0 (worst possible health state measured by the questionnaire) to 100 (best possible health state). Some studies use the SF-36 to reflect the quality of life of HT patients. It is found that when the thyroid function is normal, the quality of life of HT patients is negatively correlated with antibody levels [11, 12]. Therefore, in this study, SF-36 is also used as an observation indicator to evaluate the influence of acupuncture on HT patients. Data will be collected before the start of treatment (the baseline assessment) and at 8 and 16 weeks after randomization.

##### Hospital Anxiety and Depression Scale (HAD) [31]

HAD is a 14-item self-assessment scale that have been rated on a 4-poiont scale, used to identify and quantify the two most common forms of psychological disturbances in medical patients. And HT patients often have symptoms of mood swings. Data will be collected before the start of treatment (the baseline assessment) and at 8 and 16 weeks after randomization.

### Drug combination

The current therapeutic target of HT is to maintain the stability of thyroid function due to the lack of effective treatment for the cause of HT. Therefore, in this study, all participants have been taking exogenous levothyroxine (trade name: Youjiale) to treat hypothyroidism. Considering the influence on serum thyroid-related antibodies, taking medicine that may have an impact on antibodies, such as selenium preparations, will not be allowed. All drugs used by the participants will be recorded in detail, including the drug name, dosage and treatment course, and other information. Clinical researchers will judge the effect of the drug on the study results according to the specific situation.

### Adverse events

According to our earlier clinical observations, adverse events of acupuncture mainly involve bleeding, hematoma, fainting, and serious pain, with a close relevance to the subjective experience of patients and the penetration technique of acupuncturists. Operators shall be trained repeatedly to ensure the standard, effective, and safe operation. We will record any acupuncture-related adverse events that occur during the treatment and physicians will take necessary corresponding treatment measures. In case of serious adverse events, the clinical trial shall be interrupted immediately and effective treatment measures shall be taken. The whole process will be recorded in detail.

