## Abstract

**Background:**

The incidence rate of Hashimoto thyroiditis (HT) has gradually increased in recent years. There has been no specific etiological treatment for HT. Even though with normal level of thyroid hormone, the patients may still suffer from various clinical symptoms, such as anterior neck discomfort, fatigue, and mood swings, which seriously impair their quality of life. Acupuncture has long been used in the treatment of thyroid diseases, but there has been no related standardized clinical study as of today. This study aims to assess the feasibility, efficacy, and safety of acupuncture for HT.

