## Methods

### Objective

The objective is to assess the feasibility and effectiveness of PNHM in reducing the thyroid antibody level and improving the life quality of HT patients with hypothyroidism or subclinical hypothyroidism.

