### Study design

This study is a randomized, blank-controlled, parallel-group clinical trial. Participants will be assigned to the experimental group or the control group. Study period for both groups lasts for 33 weeks. Eligible participants will be randomly divided into the experimental group and the control group with a ratio of 1:1. The experimental group will undergo acupuncture therapy (PNHM) for 16 weeks, followed by a 16-week follow-up period and the control group will first enter an observation period for 16 weeks, followed by a 16-week compensation acupuncture therapy (PNHM). Assessments will be conducted at baseline and 8, 16, 24, and 32 weeks after randomization. The flowchart is shown in Fig. 1 and the timepoint of assessment is shown in Fig. 2.

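### Non-serious adverse events are recorded only if acupuncture-related and during treatment, so the safety aim has no randomised comparison for them

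*Protocol article*

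**What the plan says.** Safety is named as an aim twice. The abstract says "This study aims to assess the feasibility, efficacy, and safety of acupuncture for HT", and the Sample size estimation section says "This study aims to evaluate the clinical effectiveness and safety of PNHM for HT". The Objective section is narrower: "The objective is to assess the feasibility and effectiveness of PNHM in reducing the thyroid antibody level", together with quality of life, and it does not mention safety.

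The general recording rule is one sentence in the Adverse events section: "We will record any acupuncture-related adverse events that occur during the treatment and physicians will take necessary corresponding treatment measures". The sentences after it deal with serious adverse events. They are not confined to related events, to one arm or to the treatment weeks, and they call for detailed documentation.

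On exposure, the Study design section says "The experimental group will undergo acupuncture therapy (PNHM) for 16 weeks, followed by a 16-week follow-up period". Controls are first observed for 16 weeks without acupuncture and then receive PNHM for 16 weeks.

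On blinding, the Blinding section says "it is difficult to blind clinical researchers and participants" and "only two data researchers in charge of the collection, preservation, and analysis of data are blinded". Under Data collecting and monitoring, those two data researchers receive questionnaire and blood results online and have no contact with participants.

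**The concern.** The rule applies two filters, relatedness and timing, before an event is written down. This is a stated rule and not a detail left out of a condensed article, so a trial that follows it will produce data of that shape.

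An untreated control cannot have an acupuncture-related event during treatment. The control count of non-serious events in weeks 0-16 is therefore zero by construction and not by observation. Related events in controls during weeks 16-32 would be recorded, but they are events under PNHM and give no control rate. An event in the experimental arm that first appears after week 16, or that nobody links to needling when it occurs, also falls outside the rule.

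At stake is what the trial can say about tolerability. It could list the events that were attributed to needling. It could not say whether participants given PNHM had more non-serious events than those who were not, and a short list would partly reflect the rule.

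**Working it through.** **The plan's own figures.** The article states no adverse event rate or safety target, so there is no safety figure to reproduce. The sample size supplies only the denominator: 30 per group with 20% dropout leaves 30 × (1 − 0.20) = 24 completers, inside the cited 20 to 30 per group, and 24 / 0.80 = 30 per group, 60 in total. That figure is not in question.

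**Coverage of the rule for non-serious events.** Here treatment is read as the 16-week course. This reading favours the plan, because the Intervention section also uses the word for a single 20-minute session.

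| Weeks after randomisation | Experimental arm | Control arm |
|---|---|---|
| 0-16 | PNHM: related events recorded | Observation: no event can qualify |
| 16-32 | Follow-up: not covered | PNHM: related events recorded |

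- Each arm is covered for 16 of 32 weeks, or 50%.
- In weeks 0-16, the only period that compares PNHM with no PNHM by randomisation, coverage is 16 of 16 weeks in one arm and 0 of 16 in the other.
- In no period are both arms covered.

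**Illustration of the consequence.** The background rate *b* (any non-serious event over 16 weeks) and the share *s* of such events attributed to needling in the PNHM arm are both assumed. Suppose PNHM causes no excess.

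Controls with an event that full recording would find = 30 × *b*. Controls recorded under the rule = 0. Apparent PNHM rate = *b* × *s*.

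| *b* | Controls with an event (recorded) | Apparent PNHM rate, *s* = 0.25 | *s* = 0.5 | *s* = 1.0 |
|---|---|---|---|---|
| 10% | 3 (0) | 2.5% | 5% | 10% |
| 20% | 6 (0) | 5% | 10% | 20% |
| 30% | 9 (0) | 7.5% | 15% | 30% |

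With no true excess, the recorded data would show between 2.5% and 30% against 0%, depending on two quantities that the trial does not measure. The error can also go the other way: an event that PNHM did cause but nobody attributed to it is not recorded at all. The direction of bias is therefore unknown.

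**The case against.** The strongest case for the plan has four parts.

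1. **Safety is a minor aim here.** The Objective section does not name it, the Discussion gives feasibility and clinical value as the main purpose, and no between-arm safety hypothesis is stated. The events expected from earlier experience (bleeding, hematoma, fainting, serious pain) are largely procedural, and a control rate adds little for bleeding at a needle site. This stands and limits the weight of the point. It does not remove it: two sections still claim safety, and events such as fainting or pain, or events nobody expected, can occur without needling.

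2. **Much is captured elsewhere.** A reader might infer that no harm in controls would be seen, including worsening thyroid function or mood. The documents do not support that. Serious adverse events are not limited by relatedness or arm. Thyroid hormones and antibodies are primary outcomes at weeks 8, 16, 24 and 32. HAD, ThyPRO-39 and SF-36 are collected in both arms at least through week 16. All drugs used are recorded, and side effects are discussed at two-monthly workshops. The gap concerns other non-serious events.

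3. **Nobody is named as judging relatedness.** A reader might state as fact that unblinded staff who deliver the needling make the attribution. The article does not say so. It is a reasonable inference, since the clinical researchers are not blinded and the blinded data researchers have no contact with participants. The coverage table does not depend on it.

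4. **Small numbers.** A reader might express the defect as the upper bound when no event is seen, about 3/30 = 10%. That bound reflects sample size and would be the same with perfect recording. It also ignores that both groups eventually receive PNHM, so up to 60 are exposed (3/60 = 5%). It does not measure this problem.

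**Conclusion.** The point holds for non-serious adverse events. As written, the rule rules out a randomised comparison of them in weeks 0-16, leaves the experimental arm's 16-week follow-up uncovered, and may miss delayed or unattributed events. Its firm size is the coverage: 16 of 32 weeks in each arm, and 0 of 16 weeks for controls in the randomised period. The 3 to 9 uncounted controls rest on an assumed background rate of 10% to 30% and serve only as illustration.

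The conclusion assumes that the stated sentence is the operative rule for non-serious events, with no wider rule elsewhere. It does not extend to serious adverse events or to the measured outcomes, and the efficacy comparison is unaffected. The change should be made because a stated aim depends on it, and because events not recorded when they occur may not be recoverable later.

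**What to change.** Replace the rule with all-cause recording:

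- Record every adverse event, whatever its presumed cause, in both arms from randomisation to week 32.
- Ask about events with the same wording in both arms at the 8-weekly assessments. This matters because the PNHM arm is seen 3 × 16 = 48 times in weeks 0-16, which gives it far more chances to volunteer an event. The comparison between arms should rest on the common question.
- Enter relatedness as a separate field after the event is recorded, and state who judges it.
- Report the number and proportion of participants with any event by arm for weeks 0-16 as the randomised comparison. Describe weeks 16-32 separately.
- Have the existing clinical researchers collect these data on a separate form. They should not go through the online questionnaire, whose results reach the two blinded data researchers: a report of needle-site bleeding or hematoma could reveal the arm. Withhold the form from them until the outcome data are locked.

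The cost is one additional form with a relatedness field, a little extra recording, and more background events reported. Participants and collecting staff will still know the arm, so reporting bias is reduced but not removed. If the change comes part-way through the trial, the report should state which participants were covered from randomisation.
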